#### CBSST cognitive skills module

Cognitive therapy is the exclusive focus of this module but these techniques are also used throughout the other two modules. Importantly, the cognitive therapy approach focuses primarily on teaching cognitively-based coping skills for addressing obstacles to goals and upsetting feelings, rather than being based on complex formulations or schema-based work. These interventions involve practicing simple steps for modifying problematic beliefs that are compatible with other skills training approaches like SST. Less training is required for novice clinicians typical of ACT staff to become proficient at these cognitive therapy skills, compared to more complex schema or formulation-based CBT approaches. The manualized CBSST intervention is a standardized curriculum that can be easily delivered by any clinician on the ACT team.

Cognitive interventions are used to address symptoms and challenge defeatist or other maladaptive beliefs that interfere with the pursuit of goals or use of skills in real-world situations, such as negative expectancies (“It won’t be fun”), beliefs about lack of self-efficacy (“I can’t do it”), and delusions (“Spirits will harm me”). By challenging defeatist performance beliefs, consumers are more likely to engage in functional behaviors and use the skills they have. Consumers are introduced to the general concepts of CBT, including the relationship between thoughts, actions and feelings (generic cognitive model), automatic thoughts, thought challenging by examining evidence for beliefs, and mistakes in thinking (e.g., jumping to conclusions, fortune telling, all-or-none thinking). Through discussion, thought records, and homework assignments, consumers are taught to identify thoughts, examine relationships between thoughts, feelings and behaviors, and correct mistakes in thinking. Behavioral experiments are conducted inside and outside therapy sessions (homework), in order to gather evidence to evaluate beliefs. To simplify learning and help consumers remember and use cognitive techniques in everyday life, mnemonic aids are provided (e.g., laminated cards describing skills). For example, for thought challenging, we use an acronym, “The 3C’s: Catch it, Check it, Change it.” The “it” refers to a thought. Consumers are taught to use the 3C’s when they are experiencing unpleasant emotions or behaving in a way that interferes with goals (e.g., isolating, not filling out a job application, giving up on a class).

#### CBSST social skills module

The primary goal of this module is to improve communication skills and psychosocial interactions (e.g., how to ask someone for support). The predominant therapeutic technique is the use of behavioral rehearsal in role plays followed by positive and corrective feedback to shape more effective behavioral repertoires. An important focus of role plays is on interacting with roommates, friends and family, making new friends, and effectively interacting with case managers, other service providers and support persons. Expressing pleasant and unpleasant feelings, and making positive requests are emphasized to improve assertive, clear, and comfortable sharing of feelings in social interactions. Improving everyday activities and functioning are common role-play topics for these skills (e.g., asking a roommate to change their behavior; asking someone to go to the movies; assertive interactions with co-workers/ employers). Self-efficacy and performance beliefs are elicited and scaling is used before and after role plays (0–10 ratings of how successful you think you will be/were) to challenge defeatist beliefs about skills.

#### CBSST problem-solving module

As is common in SST and CBT interventions, basic problem-solving skills are taught. CBSST uses the acronym, SCALE – *S*pecify the problem, *C*onsider all possible solutions, *A*ssess the best solution, *L*ay out a plan, and *E*xecute and evaluate the outcome. The focus of this module is on developing plans to solve real-world problems and to establish the steps for achieving goals such as improving one’s living situation or finances, gaining access to transportation, finding a volunteer/paid job, enrolling in classes, increasing leisure activities, and improving relationships. Problems related to illness and disability are also addressed including, coping with symptoms and stress, remembering to take medications, and improving hygiene/health. Thoughts about the expected success/failure of plans are elicited and evidence for success/failure of attempted plans is reviewed to challenge defeatist beliefs.

### Fidelity monitoring

#### ACT fidelity monitoring

Quality of ACT services will be rated for each team by [name] (consultant) using the Dartmouth Assertive Community Treatment Scale (DACTS) [42]. The DACTS consists of 28 items, each rated on a behaviorally-anchored 5-point scale (1 = not implemented; 5 = fully implemented). The mean score for the total scale will be used as the measure of ACT team fidelity. A DACTS score of > 4.0 is considered moderately high fidelity [42]. We will examine whether ACT fidelity is related to outcomes by including it as a covariate in exploratory analyses, but we do not expect fidelity to be related to outcomes, because we expect all ACT programs to be of comparable fidelity

#### CBSST fidelity monitoring

Audio recordings of therapy sessions will be reviewed and rated for CBT fidelity using the Cognitive Therapy Scale for Psychosis (CTS-Psy) [43] and for SST fidelity using an abbreviated version of the Social Skills Training Fidelity Scale [40]. CTS-Psy ratings will be completed for sessions from all three modules because cognitive therapy interventions are used in all modules, but SST ratings will only be completed for the social skills module. The expert consultants will collect session recordings from providers on the ACT teams they will train and rate fidelity of the sessions on an on-going basis throughout the project. The consultants will meet weekly with ACT teams and provide their ratings to team members as a training tool. To incentivize learning the CBSST skills and delivery of CBSST sessions, we offered providers a certificate stating they were “high-fidelity providers” of CBSST when they delivered 10 consecutive sessions that averaged 30 or greater on the CTS-Psy. After training on the CTS-Psy, we have achieved good inter-rater reliability (intraclass correlation coefficient (ICC) = 0.85) [17].

### Clinician training

The proposed training model has been adapted to the ACT model and workload and will include: 1) an initial 1-day workshop; 2) weekly 30-minute face-to-face skill-focused supervision using coaching and role-play modeling; 3) written feedback of fidelity ratings to individual therapists and review of session audio recordings in supervision; 4) monthly “steering committee” meetings with team leaders to provide technical assistance and support for recruitment, implementation and fidelity.

The workshop will be provided by CBSST experts ([name]) and will include review of manuals and homework sheets, videotaped demonstration, and role-played/modeled delivery of CBSST. Half the members of each team will attend the workshop one day and the other half will attend a repeat of the same workshop on another day, so half the team will always be available to manage clinical care. ACT staff and leadership have indicated that a workshop longer than 1 day is not feasible. ACT staff turnover will be addressed by having annual workshops for replacement staff, and all workshop content (slides and video recordings of speakers and role plays) available to new providers online (CBSST.org). New staff will also accompany other ACT staff members to observe and co-lead CBSST sessions.

Based on pilot work, we configured a training model that minimized burden on providers by incorporating training and consultation into one of the existing daily “morning meetings” that are part of the ACT model. Providers on ACT teams usually meet each morning to share information about consumers, review and identify consumers’ progress and needs, and plan for who will meet with which consumers to address particular needs or goals. Once each week, the expert consultant will use 30 minutes of the morning meeting to provide training and consultation. Also, ACT services are team-delivered (i.e., different providers typically provide services to the same consumer), so providers of past CBSST sessions must share information with providers of future sessions (e.g., weekly homework assignments, key thoughts and themes from the last session, consumer reactions/feedback about specific skills, etc.). The daily morning meetings provide an opportunity for different providers to share this information to plan sessions.

### Outcome measures

As shown in Table 1, the primary outcome domain is psychosocial functioning. Additional outcome domains of interest include mediators of change in functioning, symptoms, and quality of services. In the following sections we discuss the key measures used for each domain.

**Table 1 Tab1:** Summary of dependent variables

Outcome domains	Dependent variables
Psychosocial functioning (Primary domain)	
1. Real-world independent living skills	1. ILSS total (primary measure)
Mediators	
1. Defeatist performance beliefs	1. DPAS total
2. Social competence	2. MASC total effectiveness score
Symptoms	
1. Negative symptoms	1. SANS factors
2. Positive and general psychopathology symptoms	2. BPRS positive symptom factor and total
Quality of services	
1. CBSST fidelity	1. CTS-Psy total and SST fidelity total
2. ACT fidelity	2. DACTS overall average
3. CBSST skill knowledge	3. CMT Total

*Abbreviations: ACT* Assertive Community Treatment*, BPRS* Expanded Brief Psychiatric Rating Scale, *CBSST* Cognitive Behavioral Social Skills Training, *CMT* Comprehensive Modules Test, *CTS-Psy* Cognitive Therapy Scale for Psychosis, *DACTS* Dartmouth Assertive Community Treatment Scale, *DPAS* Defeatist Performance Attitude Scale, *ILSS* Independent Living Skills Survey, *MASC* Maryland Assessment of Social Competence, *SANS* Scale for the Assessment of Negative Symptoms, *SST* social skills training

#### Psychosocial functioning measure

While the various psychosocial functioning measures have their own advantages and disadvantages, we selected the ILSS as the primary outcome measure because it has been the primary outcome measure in our prior CBSST studies that demonstrated the efficacy of CBSST [17, 18]. The ILSS is a 51-item self-report measure of everyday functional living skills that takes approximately 15 minutes to administer and assesses whether or not specific functioning behaviors have been performed over the past month in 10 areas: Personal Hygiene, Appearance and Care of Clothing, Care of Personal Possessions (everyday household chores), Food Preparation, Health Maintenance, Money Management, Transportation, Leisure and Community (including socialization), Job Seeking, and Job Maintenance. Responses to items in each domain are averaged, and a total score is computed as the average of all domain scores. Objective functional milestone indicators will also be collected at each assessment time point, including information on employment, educational activity, psychiatric hospitalizations, and current residential status.

#### Mediator measures

The Maryland Assessment of Social Competence (MASC) will be used in the mediator analyses. The MASC is a structured behavioral role-play assessment that measures the ability to resolve interpersonal problems through conversation [44, 45]. The MASC takes about 15–20 minutes to administer and consists of three 3-minute role-play communication scenarios (1 conversation initiation and 2 assertion), during which the consumer interacts with a live confederate who plays a role (e.g., boss) in a problem-oriented situation (e.g., asking for a work shift change). The measure has three parallel sets of scenarios for multiple administrations. Videotaped role plays are rated by blinded raters on dimensions of verbal content, nonverbal communication behavior, and overall effectiveness, which will be the primary MASC variable. The Defeatist Performance Attitude Scale (DPAS) is a 15-item self-report subscale of the commonly-used 40-item Dysfunctional Attitude Scale (DAS) [46, 47] that was derived from factor analysis. The DPAS indexes generalizes defeatist beliefs about one’s ability to perform tasks and effectiveness of social behaviors (e.g. “If you cannot do something well, there is little point in doing it at all,” “If I fail at my work, then I am a failure as a person”). Providers will document the completion of CBSST sessions, including whether homework was completed and the level of consumer participation in CBSST sessions, which will be explored as potential mediators of treatment outcome.

#### Symptom measures

Negative symptoms for the past 2 weeks will be rated using the Scale for the Assessment of Negative Symptoms (SANS) [48]. Based on factor analytic studies, the SANS ratings will be divided into experiential (Avolition/Apathy, Asociality/Anhedonia) and expressive (Affective Flattening and Alogia) factors [49]. In addition, the Expanded Brief Psychiatric Rating Scale (BPRS) [50] will be administered to index positive and general symptoms over the past 2 weeks.

#### Skill knowledge

The Comprehensive Modules Test (CMT) will be administered to assess mastery of the specific content in the three CBSST modules. The CMT was originally developed at UCLA for use with SST modules [39]. Following this format, similar questions with vignettes were developed to assess mastery of communication (max = 11), problem-solving (max = 11), and thought challenging (max = 11) skills. The CMT total score (max = 33) will be used.

### Blind assessments and inter-rater reliability

Research assistants blind to group membership will perform all assessments. We have systematic procedures in place to counsel consumers not to reveal their treatment assignment to assessors and found the blind was maintained in prior trials [17]. Assessors will receive extensive training using videotaped and practice interviews and will not complete assessments until achieving at least 0.80 inter-rater reliability.

### Analyses

Primary analyses will be based on a linear mixed-effects model for continuous data [51, 52]. We will include and test covariates that can impact functioning as appropriate (e.g., ACT team, gender, DPAS, negative symptoms). Analyses will be performed using HLM 6.06 (SSI Inc., Skokie, IL, USA). We will assess multidimensional outcomes, but selected one primary outcome (ILSS), powered the study based on this outcome, and will determine the effectiveness of the intervention based on this outcome (Aim 1).

### CBSST effectiveness analyses (Aim 1)

In the primary mixed-model analysis, the model will include a random intercept, a fixed effect for the five assessment points, and treatment group (ACT alone versus ACT + CBSST) tested in these models as predictors of the primary outcome measure, ILSS, and the secondary functioning and outcome measures (listed in Table 1). Model diagnostics will be used to determine the suitability of an autoregressive error component and nonlinear effects for assessment time.

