### Effectiveness study design (Aim 1 and Aim 2)

This is a randomized clinical trial comparing 2 treatment conditions: ACT alone, and ACT + CBSST. We will train staff (*N* = 90) from 7 ACT teams to deliver individual CBSST to consumers with schizophrenia or schizoaffective disorder (*N* = 176; based on power analysis). Consumers will be randomized within ACT teams to one of the treatment conditions and followed for 18 months, with assessments conducted every 18 weeks after baseline (5 in total). A 1-day training workshop will be provided to ACT staff who will then begin to provide CBSST to consumers randomized to ACT + CBSST, while receiving 30 minutes of weekly group consultation/training from experienced research clinicians.

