### CBSST effectiveness mediators (Aim 2)

The primary mediation analysis will be based on the recommendations of Kraemer et al. [53] using a similar linear mixed-models approach. Two conditions must be met for mediation of the treatment effect: 1) correlation between the mediator and treatment (ACT versus ACT + CBSST group effect on MASC or DPAS), and 2) relationship between the mediator and outcome (MASC or DPAS main effect or group × MASC or group × DPAS interaction on ILSS). A statistically significant effect of treatment group on the outcome is not required, according to Kraemer et al. [54], although this will be tested in Aim 1. First, we will test the effect of treatment group and the group × time interaction on the mediator (MASC or DPAS score across all available assessments). Here we are looking for a statistically significant treatment group × y time interaction. Second, we will test the effects of MASC or DPAS change (slope across available assessments) and the MASC or DPAS change × group interaction on the outcome (ILSS across all available assessments) in the model that includes group and time. Here we are looking for a statistically significant MASC or DPAS change main effect or significant MASC or DPAS change × group interactions.

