### Statistical power calculation

The methods described by Diggle et al. [54] and Hedeker et al. [55] were used to calculate power, resulting in a sample size of *N* = 176. We assumed an autoregressive covariance structure, with conservative correlation between sequential assessments set at 0.45 and up to 4 covariates in the model. We powered our primary aim (Aim 1) for our primary outcome measure (ILSS) to detect a small to medium group × y time interaction effect. For the 2 (ACT + CBSST versus ACT alone) by 5 (assessment times) mixed-model analysis evaluating the treatment group effect over the course of the entire study, a sample size of 70 per group (20 % dropout) and *α* = 0.05 2-tailed, we would have minimum power of 0.85 to detect a small to medium (0.35) group × y time interaction effect.

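### The listed terms of the primary ILSS model omit the group × time interaction on which Aim 1 is powered, and the group term as written averages in the pre-treatment baseline

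*Protocol article*

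**What the plan says.** Four places in the protocol article bear on the primary test.

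- **CBSST effectiveness analyses (Aim 1):** for ILSS and the secondary measures, "the model will include a random intercept, a fixed effect for the five assessment points, and treatment group". The only flexibility mentioned is an autoregressive error component and nonlinear time effects.
- **Statistical power calculation:** "We powered our primary aim (Aim 1) for our primary outcome measure (ILSS) to detect a small to medium group" × time interaction. The same paragraph describes a "mixed-model analysis evaluating the treatment group effect over the course of the entire study" and then gives power of at least 0.85 "to detect a small to medium (0.35) group × y time interaction effect" (the stray letter is typographical).
- **CBSST effectiveness mediators (Aim 2):** the group effect and the group × time interaction on the mediator are named as separate terms, and the interaction is the target: "Here we are looking for a statistically significant treatment group" by time interaction. The same section says that the effect of treatment group on the outcome is what Aim 1 tests.
- **Effectiveness study design:** assessments come every 18 weeks, five in total, over 18 months. Baseline must be one of the five: baseline plus four follow-ups ends at week 72, inside 18 months (about 78 weeks), whereas five follow-ups would end at week 90.

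The Analyses section makes ILSS the sole basis for judging effectiveness. Its examples of covariates do not include baseline ILSS.

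**The concern.** A model with time and group but no interaction assumes one constant group difference at all five visits. Randomisation makes the expected difference at baseline zero, so the coefficient mixes one null visit with four on-treatment visits and understates the on-treatment difference. Chance imbalance at baseline also enters the estimate, with weight 1/5, instead of being adjusted away.

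This group term is also a different quantity from the interaction in the power statement. Effectiveness rests on this one outcome, so a reader needs to know which contrast decides it and what 0.35 means on that contrast's scale. The same model is applied to the secondary outcomes, so the dilution carries over to them.

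**Working it through.** **Inputs from the power section:** 70 per group after 20% dropout, two-sided α = 0.05, five assessment times, autoregressive covariance with sequential correlation 0.45, effect 0.35, power at least 0.85. **Assumptions:** SD = 1, complete data on the 70 per group, normal approximation.

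For a contrast c over the visits, with V the AR(1) matrix and μ the true group differences:

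SE = √(2·c′Vc/70), power = Φ(|c′μ|/SE − 1.96).

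**1. The plan's own figures**

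- Sample size: 70/0.80 = 87.5, rounded up to 88 per group, 176 in total. This matches.
- Power, slope reading: the difference grows linearly from 0 to 0.70 (five-visit mean 0.35). The slope difference is 0.70/4 = 0.175 per visit; c′Vc = 0.1214, SE = 0.0589, z = 2.97, power 0.844.
- Power, post-baseline average of 0.35 without baseline adjustment: c′Vc = 0.4808, SE = 0.1172, z = 2.99, power 0.848.
- Readings that do not give 0.85: slope test with 0.35 at the last visit, 0.318; post-baseline mean minus baseline for a 0.35 step, 0.510; four-degree-of-freedom interaction test, 0.19 (linear to 0.35), 0.36 (step) and 0.67 (linear to 0.70).

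So the stated 0.85 is attainable, but on two different meanings of 0.35, and the protocol does not say which it intends.

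**2. The group term as written**

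With complete data and a random intercept, the coefficient is the difference in five-visit means: c′Vc = 10.26/25 = 0.4105, SE = √(2 × 0.4105/70) = 0.1083.

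- Step of 0.35 at all four follow-ups: 4 × 0.35/5 = 0.28, z = 2.59, power 0.73.
- Linear to 0.35: 0.35/2 = 0.175, z = 1.62, power 0.37.
- Linear to 0.70: 0.70/2 = 0.35, z = 3.23, power 0.90.

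Simulating 4,000 trials and comparing five-visit means gave 0.281 with power 0.735 for the step, and 0.174 with power 0.364 for linear to 0.35.

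If the optional autoregressive error is adopted, the end visits gain weight. Baseline then carries 1/(2 + 3 × 0.55) = 0.274, so the step is estimated as 0.254 with power 0.665.

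**3. Baseline-adjusted mean of the four follow-ups**

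The covariance of baseline with the follow-up mean is (0.45 + 0.2025 + 0.0911 + 0.0410)/4 = 0.1962. Adjusted variance = 0.4808 − 0.1962² = 0.4423, SE = 0.1124.

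- Step: 0.35/0.1124 = 3.11, power 0.876.
- Linear to 0.35: mean 0.219, z = 1.95, power 0.49.
- Linear to 0.70: mean 0.4375, z = 3.89, power 0.97.

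**4. Side by side**

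| True difference | Written coefficient | Power, as written | Power, interaction | Power, adjusted four-visit mean |
|---|---|---|---|---|
| 0.35 at every follow-up | 0.28 | 0.73 | 0.51 (follow-up mean minus baseline) | 0.876 |
| Linear to 0.35 | 0.175 | 0.37 | 0.32 (slope) | 0.49 |
| Linear to 0.70 | 0.35 | 0.90 | 0.84 (slope) | 0.97 |

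**5. Sensitivity to the covariance**

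Under compound symmetry at 0.45, which the plan does not assume, the second and third power columns change places in rank: written term against interaction is 0.60 against 0.70, 0.28 against 0.60, and 0.79 against 0.99. The adjusted mean has power 0.92 for the step.

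**The case against.** The strongest reply is that the Aim 1 sentence is shorthand. It says what the model will include, not that nothing else enters. The power section plainly has an interaction in mind, and Aim 2, called a similar mixed-model approach, lists one. The article condenses a fuller protocol, and an SAP may settle the matter. This stands in part: the text does not prove that the interaction will be left out. It does not settle the question the other way either, because Aim 2 separates the two terms and then describes Aim 1 by the group effect alone, and the power paragraph uses both descriptions.

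Four stronger readings that a reader might infer are not supported.

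- **That restoring the interaction recovers power.** Under the plan's AR(1) assumption, the written group term has more power than the bare interaction in all three shapes. The ordering depends on the covariance, as the sensitivity check shows.
- **That the primary test is underpowered in general.** If 0.35 is the average under linear divergence to 0.70, the written test has power 0.90, above the stated minimum.
- **That the test is invalid.** The coefficient is unbiased for the five-visit average, chance baseline imbalance has expectation zero and is already in the SE, and type I error is not inflated.
- **That the test could be picked after the data are seen.** That would require an SAP silent on the point, which this article cannot show.

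The four-visit mean is also one reasonable contrast among several; a slope or a final-visit difference could be defended.

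**Conclusion.** The point holds as an inconsistency with a measurable consequence. The listed primary model lacks the term on which Aim 1 is powered, and the sections name different tests for the only confirmatory outcome. Followed literally, the group coefficient understates the on-treatment difference: by 20% for a constant effect after baseline (0.28 for 0.35, power 0.73), and by half relative to the final visit under linear divergence.

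These sizes rest on SD 1, 70 complete participants per arm, AR(1) at 0.45 and assumed effect shapes, since the scale of 0.35 is not given. Under the plan's covariance, a baseline-adjusted post-baseline contrast has more power than the written term in every shape examined, which a bare interaction does not. The defect is dilution and inefficiency in an ambiguously specified test, not a risk of false positives.

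**What to change.** Reconcile the Aim 1 and power sections before unblinding.

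- **Model:** use categorical time with group × time and group means constrained equal at baseline. Alternatively, take the four follow-ups as outcomes with baseline ILSS and its interaction with time as covariates. The two are close but not identical when data are missing, so choose one.
- **Contrast:** name a single primary contrast, for example the mean difference over the four post-baseline assessments, and report the final-visit difference as secondary.
- **Power:** define 0.35 on that contrast's scale and restate the 0.85. If 0.35 is meant as the post-baseline average, the unadjusted calculation gives 0.848 and the adjusted one 0.876, so N = 176 stands. If it is meant as the final-visit difference under linear growth, power for this contrast is about 0.49, and the plan should say so.

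The cost is rewording two sections, with no new data or participants. The Trial status section reports that assessment was still under way.
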